#### Sample size

As this is a feasibility study, no formal sample size calculation has been undertaken. However, Sim and Lewis [46] recommend at least 50 participants for this type of study. Accordingly, approximately 25 participants will be recruited into each arm, giving a total sample size of 75 patients. Our sample size compares favourably to previous trials investigating treatment of idiopathic BPPV [47, 48] and other feasibility studies [49, 50]. We will use secondary outcome measures to inform a sample size calculation for a future RCT.

A sample of up to ten patients who declined to take part in the study will be interviewed to examine their reasons for declining and therefore optimise recruitment strategies for a future study. Approximately ten therapists and 18 patients participating in the trial will also be interviewed at the end of the trial to explore intervention acceptability. Sample sizes for the qualitative component were drawn up following consultation of relevant guidance [51] which advocates an emphasis on sampling diversity as well as size in feasibility studies.

### Phase 2—interviews with participants and therapists

The aim of this phase will be to explore the feasibility of the trial from a participant and therapist perspective using face to face, individual interviews. A topic guide will be used to structure the interviews and will examine participants’ and therapists’ views on the study design and their experience of recruitment processes, assessments, outcome measures, the intervention itself and follow-up assessments. Data from this phase will be utilised to refine the study procedures to maximise recruitment for a subsequent RCT.

Potential participant interviewees will be purposively sampled at the 12-week follow-up timepoint. A sample of approximately 18 participants (6 from each treatment arm across all centres) will explore the thoughts and views of those taking part in the trial. Additionally, up to 10 participants who declined to participate in the study will be invited to take part in individual interviews to explore reasons for non-participation. They will be interviewed face to face or by telephone, according to preference. Up to ten therapists participating in the trial across all centres will be asked to consent to individual interviews.

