**Method:**

A multi-centre randomised mixed methods feasibility study design was employed. We aim to recruit approximately 75 acute TBI patients across a range of clinical severities, from three major trauma centres in London. Patients will be randomised to one of three treatment arms: (1) therapist-led manoeuvres, (2) patient-led exercises and (3) advice. Participants will be re-assessed by blinded outcome assessors at 4 and 12 weeks. Acceptability of the intervention will be obtained by patient interviews at the end of their treatment and therapist interviews at the end of the study. Primary outcomes relate to feasibility parameters including recruitment and retention rates, adverse events and intervention fidelity. We will also aim to provide a more accurate estimate of the prevalence of BPPV in TBI cases on the trauma ward.

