### Aim and objectives

The primary aim of this study is to evaluate the feasibility of conducting a future randomised controlled trial (RCT) investigating the effectiveness of treating BPPV in acute TBI.

Primary objectives focus on feasibility outcomes and will aid the design of a future definitive trial:
To establish trial recruitment rates, including the willingness of patients to be randomised to a treatment armTo determine trial retention rates, the fidelity of the intervention, its acceptability to participants and clinicians and any missing dataTo explore the incidence of adverse events

Secondary objectives will also support the design of a future RCT. They include:
An estimate of the prevalence of BPPV in acute TBICalculating effect sizes for primary and secondary outcome measures to thereby inform sample size estimates for future studiesExamining the relationship between vestibular perception, balance impairment and clinical outcome

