#### Trial progression criteria

Trial progression criteria will be used to determine whether it is appropriate to move forwards to a RCT. Criteria include:
60% of those screened eligible for inclusion.Initially 30% of eligible patients are expected to consent to participate in the study, rising to 50% of those eligible consented as the research team gain confidence with consenting procedures.≤ 40% drop out rate.

Thresholds for participants consenting have been informed from previous feasibility studies in acute TBI [57, 58] and reflect some of the challenges of recruiting acute TBI patients [59].

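### Trial interviewees are chosen at 12 weeks with no stated route to those who leave earlier, so acceptability risks resting mainly on those who stayed; interview timing also needs reconciling

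*Protocol article*

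**What the plan says.** All references are to the protocol article.

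- **Aim and objectives.** One primary objective groups retention, fidelity and missing data with the intervention and "its acceptability to participants and clinicians".
- **Phase 2.** "Potential participant interviewees will be purposively sampled at the 12-week follow-up timepoint". About 18 participants are to be interviewed, six from each arm, across all centres. Up to ten people who declined entry are also interviewed, face to face or by telephone as they prefer. The topic guide includes views on the follow-up assessments.
- **Abstract, Method.** "Acceptability of the intervention will be obtained by patient interviews at the end of their treatment and therapist interviews at the end of the study".
- **Sample size.** About ten therapists and "18 patients participating in the trial will also be interviewed at the end of the trial to explore intervention acceptability".
- **Outcome measures.** Timepoint 2 is set at 12 weeks after treatment.
- **Trial progression criteria.** One criterion for moving to a full trial is "≤ 40% drop out rate".

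**The concern.** Two things stand out.

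The first is who gets heard. Selection of trial interviewees is tied to a point about three months after treatment. People who found the intervention or the follow-up hard to accept are plausibly over-represented among those who have left by then. The decliners have their own route, but they received no intervention and cannot speak to its acceptability. The group in between, randomised and then gone, has no route named. If only stayers are interviewed, acceptability will look better than it was. A poor retention figure would then come with little explanation, although the interviews are meant to refine procedures for the next trial.

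The second is when. The sections do not agree on the timing of patient interviews, and timing decides both what a participant can comment on and who is still reachable.

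**Working it through.** **1. The plan's own figures.** Randomised: 3 arms × 25 = 75. Participant interviews: 3 arms × 6 = 18. Both match the text.

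**2. Is the number of interviews at risk?** At the 40% limit, 0.40 × 75 = 30 leave and 75 − 30 = 45 remain, or 45 / 3 = 15 per arm if losses are even. Six interviews per arm stay attainable. The issue is who is represented, not how many.

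**3. How many leavers might be missed?** The documents give no expected drop-out, so a range is assumed, with the progression limit at the top. The last column is 18 × d, the number of leavers in 18 interviews if they were represented in proportion.

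| Drop-out d | Leavers, 75 × d | Stayers | Leavers in a proportionate 18 |
|---|---|---|---|
| 10% (assumed) | 7.5 | 67.5 | 1.8 |
| 20% (assumed) | 15 | 60 | 3.6 |
| 30% (assumed) | 22.5 | 52.5 | 5.4 |
| 40% (progression limit) | 30 | 45 | 7.2 |

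If in practice only those still in follow-up at week 12 are approached, the last column becomes 0 in every row. Purposive sampling does not aim at proportionality, so the column shows scale and is not a target.

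**4. Which routes are stated?**

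| Group | Received an intervention? | Interview route stated? |
|---|---|---|
| Declined entry | No | Yes, up to 10, face to face or telephone |
| Randomised, in follow-up at week 12 | Yes | Yes, about 18 |
| Randomised, stopped treatment but still in follow-up | At least in part | Yes, within the 18, though not named |
| Randomised, left follow-up before week 12 | Yes, at least in part | None named |

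**5. Timing, side by side.**

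- The Abstract interviews patients when their treatment ends. Under Interventions, therapist-led treatment ends after at most three sessions, and the exercises run for 2 weeks.
- Phase 2 selects interviewees at a timepoint defined as 12 weeks after treatment.
- The gap is therefore about 12 weeks. If the 12 weeks in the exercise arm are counted from the teaching session and the 2 weeks of home exercise count as treatment, it is 12 − 2 = 10 weeks. On either count the two statements cannot both hold.
- An interview when treatment ends comes before the 4-week and 12-week assessments, so it cannot cover the follow-up assessments listed in the Phase 2 topic guide.
- The Sample size section has patients who "will also be interviewed at the end of the trial to explore intervention acceptability". This may mean each participant's last visit, which agrees with Phase 2, or the close of the whole trial, which does not.

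The result is one firm contradiction (Abstract against Phase 2) and one ambiguity (Sample size).

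**The case against.** The strongest reply is that the text excludes nobody. It names a timepoint, not attendance at a visit, and that may fix when selection happens without limiting who can be selected. Sampling is purposive, the Sample size section cites guidance that stresses diversity, and detailed criteria are often left to a full protocol. This stands in part: a reader might infer that leavers cannot inform acceptability, and the documents do not support that. But the article does fix the time of selection, the spread by arm and centre, and a dedicated route for decliners. The missing counterpart for leavers is therefore more than an omitted detail.

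Next, stopping treatment is not the same as leaving follow-up. Treatment is short, and the planned analysis includes patients whether or not they complete it. Someone who disliked the manoeuvres may still be present at week 12, and someone lost later may have had no complaint about the intervention. This stands and narrows the gap to those who left follow-up.

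Third, other evidence bears on acceptability: reasons for stopping, an exercise diary, drop-out rates, adverse events and therapist interviews. This helps but does not close the gap. Reasons for stopping are described under the therapist-led arm and concern the intervention, not departure from follow-up. Drop-out counts show how many left, not why. Therapists give the clinicians' view, and the objective asks for the participants' view as well.

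Finally, it is tempting to put a number on the bias, as a gap between true and reported percentages who find an arm acceptable. The documents do not support that. The interviews are analysed by a Framework approach and estimate no percentage, and any acceptability rates for stayers and leavers would be invented.

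**Conclusion.** The point holds as a risk of selection towards stayers plus a timing conflict that must be reconciled. It is worth correcting, since it touches a primary objective, but it does not threaten the trial's quantitative results.

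The size of the selection cannot be computed from the documents. Over drop-out of 10% to 40%, between about 2 and 7 of 18 interviewees would be leavers under proportionate representation, against none if only those still in follow-up are approached. This rests on the assumed drop-out range and on the plan being applied as its wording suggests.

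Three stronger readings should be set aside. The 40% is a progression limit, neither a forecast nor a cap, so it does not show that 30 participants will be missed. The timings are not three incompatible rules, because the wording under Sample size may simply mean the 12-week visit. And a worry that interviews could cue participants or assessors before the blinded assessments arises only under the Abstract's timing, whereas the loss of leavers arises mainly under the Phase 2 timing, so the two harms should not be added together.

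**What to change.** 1. State in Phase 2 that all randomised participants are eligible for the 18 interviews, whether or not they remain in follow-up.
2. Add early withdrawal from treatment or from follow-up as a purposive sampling criterion within each arm, beside arm and centre. The number of places is for the investigators to decide.
3. Offer leavers the telephone option already given to decliners.
4. Interview stayers after their 12-week assessment and leavers after they withdraw.
5. Make the Abstract, Sample size and Phase 2 sections state the same timing, and say whether the end of the trial means the participant's last visit or the close of the study.
6. Report how many leavers were invited and how many agreed, so that readers can see whose views the acceptability finding rests on.

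The cost is protocol wording and modest effort to contact leavers; the number of interviews does not change. Some leavers will refuse, so the selection will be reduced, not removed.

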#### Planned data analysis

Results will be reported descriptively to chart demographic and observational data. Participant recruitment/retention data will be reported using pilot and feasibility CONSORT guidelines [52]. An estimate of the prevalence of BPPV in acute TBI will be reported with 95% confidence intervals. The analysis will be undertaken on an ‘intention to treat’ basis, i.e. analysis will include all patients at the end of the study, whether or not they complete the intervention. We will assess the predictors of (i) return to work and (ii) BPPV at 3 months via a binary multiple logistic regression with predictors: DHI score, intervention group, duration of post traumatic amnesia and the presence of skull fracture. Our projected sample size of 75 patients should be sufficient to test these regression models given that each one has four variables. As there are two regression models, which both use the same predictor variables, the alpha will be adjusted (*α* = .025) based on the Bonferroni correction. We do not expect to demonstrate significant results from this data; rather, it will be used to calculate effect sizes for future prospective treatment studies.

Qualitative data will be transcribed verbatim and analysed using a Framework approach [53, 54]. This type of analysis uses a series of interconnected stages which enables the researcher to move back and forth across the data until a coherent account emerges. Following familiarisation with the transcripts, a framework is developed according to key issues or themes, into which data is then indexed. Data is then summarised by category and charted using the final coding index. Finally, key characteristics and differences between data are identified, allowing the generation of concepts, connections and relationships.

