**Discussion:**

The multi-centre nature of our feasibility study will inform the design of a future prospective treatment trial of BPPV in acute TBI. Important parameters we will obtain from this study, key for designing a future prospective treatment study, include estimating the prevalence of BPPV in TBI patients admitted to UK major trauma wards, and elucidating both patient and care-provider barriers in delivering BPPV treatment.

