#### Assessment

Eligible patients who consent to take part in the study will be assessed by a ward therapist for BPPV using a Dix Hallpike manoeuvre (Fig. 3), which is the gold standard diagnostic test [25]. Therapists (occupational therapists and physiotherapists) will be trained to undertake such manoeuvres prior to the study commencing.

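### Prevalence of BPPV is claimed for TBI patients on trauma wards, but only eligible, consenting inpatients are tested, so the planned 95% CI cannot support that claim without an assumption about the untested

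*Protocol article*

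**What the plan says.** The population claimed appears in several places in the protocol article.

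- Abstract, Method: "We will also aim to provide a more accurate estimate of the prevalence of BPPV in TBI cases on the trauma ward".
- Abstract, Discussion: among the parameters described as key for designing a later treatment study is "estimating the prevalence of BPPV in TBI patients admitted to UK major trauma wards".
- Aim and objectives: a prevalence estimate in acute TBI is a secondary objective.
- Planned data analysis: "An estimate of the prevalence of BPPV in acute TBI will be reported with 95% confidence intervals". No restriction to a subgroup is attached.

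The population tested is set elsewhere.

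- Assessment: "Eligible patients who consent to take part in the study will be assessed by a ward therapist for BPPV".
- Eligibility criteria: exclusions include a Glasgow Coma Score under 14, medical instability, current substance abuse, certain psychiatric histories and injuries that prevent neck extension. A consultee may advise where the patient cannot consent.
- Abstract, Method: recruitment is from three London centres.

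Trial progression criteria give the rates that link the two. The eligibility threshold is "60% of those screened eligible for inclusion". On consent, the article states: "Initially 30% of eligible patients are expected to consent to participate in the study". It then looks for half of the eligible to consent once staff are more practised.

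**The concern.** A prevalence interval describes the group that was sampled. Here that group is reached through two filters, eligibility and consent to a treatment trial, and the estimate is then attributed to a wider group that was not sampled. Both filters could be related to BPPV. Several exclusions concern injury severity or type, and the Background attributes post-traumatic BPPV to mechanical displacement during the head injury itself. Consent to a BPPV treatment trial might also depend on symptoms, although the Background notes that vestibular agnosia can suppress the reporting of dizziness. The direction of any selection is therefore open.

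At stake is the meaning of a named secondary result. The Background cites 11% to 28% in sub-acute TBI and up to 55% in acute pilot data, and the study promises a more accurate figure. A selected estimate presented as ward prevalence, with an interval that carries sampling error alone, would appear to settle that question more firmly than the design allows.

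**Working it through.** **Inputs from the article.** Randomised total 75 (Sample size); only BPPV-positive patients are randomised (Randomisation); 60% of screened eligible, and 30% rising to 50% of eligible consenting (Trial progression criteria); earlier prevalence figures of 11% to 28% and up to 55% (Background).

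**Assumptions.** All consenting patients are tested; recruitment reaches 75 positives; prevalence p among the tested is 55%, with 28% and 11% as alternatives; the interval is two-sided Wald with z = 1.96, since the article does not name a method.

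**The plan's own figure.** 3 arms × 25 = 75, which reproduces. The article gives no tested number and no interval width for prevalence.

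**Step 1, tested share f of screened patients.** f = P(eligible) × P(consent).
- At the initial consent rate: 0.60 × 0.30 = 0.18.
- At the later rate: 0.60 × 0.50 = 0.30.

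So 70% to 82% of screened patients would be untested.

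**Step 2, sampling interval in the tested group.** n = 75 / 0.55 = 136.4, so 137. Half-width = 1.96 × √(0.55 × 0.45 / 137) = 8.3 points. A Wilson interval on 75/137 is 46.4% to 62.8%, so the choice of method hardly matters.

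**Step 3, bias for the screened population.** Let d be the difference in prevalence between untested and tested patients. The screened-population value is f·p + (1 − f)(p + d) = p + (1 − f)·d, so the bias has size (1 − f)·|d|. It equals the half-width when |d| = half-width / (1 − f).
- f = 0.18: 8.33 / 0.82 = 10.2 points.
- f = 0.30: 8.33 / 0.70 = 11.9 points.

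**Step 4, coverage of the screened-population value** (normal approximation, p = 55%, n = 137).

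| Assumed size of d | f = 0.18 | f = 0.30 |
|---|---|---|
| 0 | 95% | 95% |
| 5 points | 84% | 87% |
| 10 points | 51% | 62% |
| 20 points | 3% | 9% |

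The documents supply no value of d; these are scenarios only.

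**Step 5, what the data say with no assumption.** If none or all of the untested have BPPV, the screened-population value lies between f·p and f·p + (1 − f).
- f = 0.18: 9.9% to 91.9%, 82 points wide.
- f = 0.30: 16.5% to 86.5%, 70 points wide.

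The sampling interval is about 17 points wide. The bounds are extreme by construction. They show how much of a ward-level statement would have to come from assumption.

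**Step 6, sensitivity to p.** At p = 28%, n = 268, the half-width is 5.4 points, and d of 6.6 (f = 0.18) to 7.7 points (f = 0.30) matches it. At p = 11%, n = 682, the half-width is 2.3 points, and d of 2.9 to 3.4 points matches it. Lower prevalence means more patients tested, a tighter interval, and a smaller difference needed to displace it.

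**The case against.** The strongest reply is that the interval is correct for what it measures. For eligible, consenting patients its width is right, and if tested and untested patients do not differ it covers the screened-population value at 95% too. This stands. A reader might infer that the interval will be far too narrow; the documents do not show that, because they give neither the size nor the direction of any difference.

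The rates also need care. The 60% is a progression threshold, not a forecast, and the 50% is a level to be reached. Only the initial 30% is plainly an expectation. The article does not define who is screened, so screened patients need not be all TBI admissions. The 18% to 30% is therefore indicative.

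A reader might also give the untested a prevalence of 28% and conclude that the ward value is 33% to 36% rather than 55%. That is not supported: the 28% comes from sub-acute patients, and nothing links it to acute patients who are ineligible or decline. Nor does it follow that a later trial's recruitment would be mis-sized. For a trial with a similar eligibility and consent process, positivity among those tested is the input needed, and this study measures it.

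It is also fair that patients who cannot extend the neck cannot have this test under any plan, that CONSORT reporting of recruitment is promised, and that up to ten decliners will be interviewed. The detail of tables and sensitivity analyses may sit in a fuller document. None of this changes the stated claim. The claimed and tested populations are both fixed in the article, and ten interviews do not estimate selection bias.

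**Conclusion.** The point holds as a mismatch between the population claimed and the population tested. By the article's thresholds and consent rates, some 70% to 82% of screened patients would be untested. The planned interval, about ±8.3 points if 55% of 137 are positive, reflects sampling error among eligible, consenting inpatients at three London centres. It supports a ward-level or UK-wide statement only with an added assumption about everyone else. At that prevalence, a tested-untested difference of 10 to 12 points either way would give a bias as large as the half-width.

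The finding is not that the estimate is biased, nor that the interval is wrong for the group tested. The size of any bias is unknown, and so is its sign. The conclusion rests on the stated rates being roughly met and on the assumed 55%. The mismatch itself rests on neither.

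**What to change.** 1. In the abstract, the secondary objective and Planned data analysis, state the estimand as Dix Hallpike-positive BPPV among eligible, consenting inpatients at the participating centres.
2. Define the screened pool, and report the numbers and fractions screened, eligible, consented and tested beside the prevalence estimate.
3. Before any statement about the ward, compare tested with untested patients on whatever the screening data hold, including the reason for not being tested, and give a sensitivity range: p + (1 − f)·d over a stated span of d in both directions, using the observed p and f. Do this separately for all eligible and for all screened patients.

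The cost is wording, one descriptive table and a short calculation, with no change to recruitment or testing. The drawback is a less general headline claim. The comparison in item 3 is limited to what may be recorded on patients who did not consent.

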## Background

Traumatic brain injury (TBI) is the most common cause of long-term disability in working age adults [1]. Indeed, in England and Wales, it is estimated TBI results in 1.4 million emergency visits per year [2], costing the economy £15 billion [3] and resulting in a significant impact on health-related quality of life for patients and carers [4]. Amongst the plethora of impairments experienced by TBI survivors, vestibular features or complaints of dizziness and/or imbalance are common, with large numbers of patients remaining symptomatic at 5-year follow-up [5].

The impact of dizziness on TBI survivors can be varied and burdensome, affecting physical, psychological and socioeconomic domains [6]. Acute and long-lasting dizziness can directly affect physical health, with implicit links to imbalance and therefore risk of falls [7, 8], which affect half of community-dwelling TBI survivors [9, 10]. The well-documented impact of falls on physical and psychological morbidity, mortality [11] and healthcare resource consumption [12] necessitates risk factors such as dizziness be appropriately managed. Imbalance and dizziness can also impair mental wellbeing, as demonstrated by studies describing direct links between the vestibular system and brain areas involved in emotional and cognitive processing [13–15]. Further, Chamelian et al. (2004) demonstrated dizziness to be an independent predictor of return to work, reporting only a third of dizzy patients had returned to work at 6 months compared to three quarters of patients without dizziness [16]. The implications of long-term unemployment not only include a socioeconomic burden for patients and their families, but also involve a wider impact on work productivity and costs for employers and society. Indeed, findings from a large observational study demonstrated the majority of patients with dizziness had reduced their workload and lost working days at just 3 months post onset of symptoms [17]. Therefore, the complex interplay between dizziness, physical health, neuropsychiatric function and socioeconomic factors provides the rationale for enhancing early diagnosis and treatment of dizziness.

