#### Interventions

Participants will be randomly allocated to one of three arms: (1) therapist-led repositioning manoeuvres, (2) patient-led exercises, or (3) advice.
*Therapist-led repositioning manoeuvres*

Repositioning manoeuvres are physical movements of the head and body typically used to treat idiopathic or traumatic BPPV [25]. Ward therapists will be taught to perform repositioning manoeuvres as per clinical guidelines [25]. Those diagnosed with BPPV affecting both left and right sides will be treated with the most symptomatic side first (or the side with the most intense nystagmus if the participant is not symptomatic). A repeat diagnostic test will be subsequently performed to determine the success of the intervention. The number of manoeuvres required for resolution of BPPV will vary between participants. If acceptable, the therapist will continue completing manoeuvres, up to a maximum of three manoeuvres per session, and a maximum of three sessions (over subsequent days where applicable). Participant discomfort, nausea, or vomiting would be indications to cease treatment. Any adverse events or reasons to stop the intervention will be recorded.
2.*Patient-led exercises*

Patient-led or Brandt-Daroff exercises are a form of physical self-treatment involving repeated movements of the head and trunk prescribed by clinicians as an alternative to, or in tandem with, repositioning manoeuvres. The National Institute of Clinical Evidence suggest Brandt-Daroff exercises as a treatment option for idiopathic BPPV [30], although their effectiveness is unknown post TBI.

Ward therapists will teach participants and carers (where required) the Brandt-Daroff exercises. A repeat diagnostic test will be completed. Following treatment, participants will be instructed to complete the exercises twice per day for 2 weeks, using a standardised, written exercise sheet. Participants will be asked to complete a home diary to record their adherence with the exercises.
3.*Advice*

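### Counting 75 patients against four variables does not show that the two logistic models are adequately supported: each has five slopes and, at best, 7.5 events per slope

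*Protocol article*

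**What the plan says.** Planned data analysis specifies two binary multiple logistic regressions, one for return to work and one for BPPV at 3 months. Both use the same four predictors: Dizziness Handicap Inventory (DHI) score, intervention group, duration of post-traumatic amnesia and presence of skull fracture. On adequacy it says: "Our projected sample size of 75 patients should be sufficient to test these regression models given that each one has four variables". No event rate, event count or power accompanies this. The section then says that significant results are not expected and that the data will be used to calculate effect sizes for later treatment studies.

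Four other places supply the figures that matter:

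- Sample size: "As this is a feasibility study, no formal sample size calculation has been undertaken", and "approximately 25 participants will be recruited into each arm, giving a total sample size of 75 patients". Study monitoring lists recruitment of 75 as a reason to stop, so nothing is added for dropout.
- Interventions: "Participants will be randomly allocated to one of three arms".
- Trial progression criteria: the upper limit for going on to a full trial is a "40% drop out rate".
- Background: a cited study of dizziness after brain injury is described as "reporting only a third of dizzy patients had returned to work at 6 months", against three quarters of patients without dizziness.

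**The concern.** The only reason offered for adequacy is the number of patients set against the number of variables. That comparison ignores three things. In a logistic model the information comes mainly from the rarer outcome, so 75 patients with 25 events carry much less than 75 suggests. A three-level factor uses two coefficients, so four variables mean five slopes. And 75 is the number randomised, whereas the outcomes are measured at 3 months, after any dropout.

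What is at stake is how the results are used. The article does not rely on these models for a treatment conclusion, but it does intend them to yield effect sizes for the next trial. An effect size with a very wide interval is a poor planning input, and a printed statement that the sample was sufficient invites readers to trust it more than they should.

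**Working it through.** **The plan's own reasoning.** 75 / 4 = 18.75 patients per variable; with five slopes, 75 / 5 = 15. Either would pass a rule of 10 or 15 patients per variable (four variables would need 40 or 60). The article names no rule, so this is only a guess at its basis. The alpha reproduces: 0.05 / 2 = 0.025.

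**Slopes per model.** DHI 1 + arm (3 − 1) = 2 + amnesia duration 1 + skull fracture 1 = 5, plus an intercept. DHI and amnesia duration are taken as linear.

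**Patients analysed.** No dropout: 75. At the 40% limit: 75 × (1 − 0.40) = 45.

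**Events per slope** = min(events, non-events) / 5, where events = patients analysed × outcome rate.

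| Outcome rate | 75 analysed: events (per slope) | 45 analysed: events (per slope) |
|---|---|---|
| 10% (assumed) | 7.5 (1.5) | 4.5 (0.9) |
| 20% (assumed) | 15 (3.0) | 9 (1.8) |
| one third (Background, return to work) | 25 (5.0) | 15 (3.0) |
| 50% (most favourable possible) | 37.5 (7.5) | 22.5 (4.5) |

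The one-third row is the only one whose rate comes from the document, and it concerns return to work. The article gives no rate for BPPV at 3 months, so that model is covered by the assumed range of 10% to 50%. Above 50% the non-events become the smaller group and the ratio falls again. Hence 7.5 is the ceiling at any rate for either model, and it needs zero dropout.

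For scale, the conventional benchmark of 10 events per coefficient (not from the article) would need 10 × 5 / (1/3) = 150 analysed at a one-third rate, or 100 at 50%. A lenient benchmark of 5 is met at one third only with no dropout at all.

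**What this means for an arm odds ratio.** The five-slope model was simulated, 2,000 runs per setting, under these assumptions: true odds ratio 2 for each active arm against advice; log odds effects of 0.4 and −0.4 per standard deviation for the two continuous predictors; −0.5 for a binary predictor present in 30%. Fits that separated or failed were left out of the spread.

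| Analysed, rate | Central 95% of estimated odds ratios | Separated or failed | Power at alpha 0.025 |
|---|---|---|---|
| 75, 50% | 0.57 to 8.19 | 0% | 14% |
| 75, one third | 0.56 to 10.47 | 0.25% | 11% |
| 45, one third | 0.30 to 16.24 | 3.75% | 4% |

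Average bias is small next to this spread: with 75 patients at one third, the mean log odds ratio was 0.79 against a true 0.69, with a standard deviation of 0.76. The main problem is imprecision.

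**The case against.** The strongest defence is that little hangs on these models. The trial is a feasibility study whose primary outcomes are recruitment, retention, fidelity, completeness and adverse events. It disclaims a formal sample size, no progression criterion uses the regressions, and the article already says it does not expect significance. All of that stands, and it limits how serious the point is. It does not rescue the sufficiency sentence, because the stated use of the results is to supply effect sizes, and that use depends on precision.

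Several stronger readings are tempting but not supported:

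- **That the plan's own figures leave 15 events in both models.** The 40% is a tolerated limit, not an expected dropout. The one third is a cited 6-month rate in dizzy patients, not a planning assumption for 3 months. It says nothing about BPPV. With the higher rate cited for patients without dizziness, a mixed sample could come nearer to 50%, which is why the best case is shown.
- **That 45 analysed breaches the source cited for at least 50 participants.** The article does not say whether that recommendation means recruited or analysed.
- **That the return-to-work model loses everyone not employed before injury.** Eligibility has no employment criterion, but how the Work Quality Index becomes a binary outcome, and for whom, may be set out in a fuller document. The denominator of the cited one third is also unknown.
- **That an alpha of 0.025 fails because each model has several coefficients.** The article claims a correction for two models only, and that division is right.
- **That the models will often fail to fit.** At 15 events about 4% of simulated fits separated or failed. The rate reached about 23% only with maximum dropout and an assumed one-fifth event rate.

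**Conclusion.** The sufficiency claim is wrong as written, because patients per variable is the wrong measure for a logistic model. The fair statement for return to work is about 15 to 25 events, or 3 to 5 per slope, resting on the cited one-third rate and dropout between 0% and 40%. For BPPV it is 0.9 to 7.5 per slope, resting on an assumed rate of 10% to 50%. The conclusion does not hinge on either rate: at the most favourable rate with no dropout, the simulated arm odds ratio still ranged from about 0.6 to 8 around a true value of 2, given the simulation assumptions listed above.

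This should be corrected. It concerns a secondary analysis in a feasibility trial and does not threaten the primary objectives.

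**What to change.** Delete the sufficiency sentence and replace it with text along these lines:

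> No sample size was calculated for these models. Between 45 (dropout at the progression limit) and 75 (no dropout) patients are expected to be analysable. At a one-third return-to-work rate this gives about 15 to 25 events for five slopes. The rate of BPPV at 3 months is unknown; 10% to 50% would give between 4.5 and 37.5 events. Intervention group will enter as two indicators with advice as reference. Both models will be fitted by Firth penalised likelihood with the planned predictors. Odds ratios will be reported with 95% confidence intervals, labelled exploratory, and will not be treated as precise inputs for sizing a future trial.

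Firth estimation gives finite estimates under separation and reduces small-sample bias, so all four planned predictors can stay. It does not create information, and the intervals will remain wide; the exploratory label is therefore as important as the method. The alpha adjustment for two models needs no change on this account.

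The cost is wording and an analysis option only, with no change to recruitment, data collection or patient procedures. The downsides are small: the stated adequacy becomes less favourable, and penalised estimates are slightly shrunk towards no effect.
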